### Outcome measures

Primary outcome measures will be: (1) smoking behavior across a 24-hour period, defined by the number of cigarettes smoked (measured by self-report and returned cigarettes) and (2) the average volume of smoke inhaled per cigarette (measured by the smoking topography device). Secondary outcomes measured pre- and post-intervention will be smoking urges (as measured by the QSU-brief), motivation to quit smoking (as measured by the Contemplation Ladder), and perceived taste of the cigarettes. Secondary outcomes measured post-intervention, only by self-report, will be experience of smoking from the cigarette pack, overall experience of smoking, attributes of the cigarette pack, perceptions of the on-packet health warnings, behavior changes, views on plain packaging, and the rewarding value of smoking (as measured by the concurrent choice and transfer task).

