### Study objectives and hypotheses

We propose a randomized controlled trial to assess the impact of plain packaging compared to branded packaging on cigarette smoking behavior over the course of a typical smoking day. We hypothesize that those participants randomized to receive plain packs compared to branded packs will smoke fewer cigarettes and will have reduced exposure to cigarette smoke over the course of the day. We will explore whether these effects are most pronounced among female smokers.

Similar to the previous real-world studies, we will also assess participants’ perceptions of the cigarette packs and the cigarettes they contain, and their attitudes to smoking, using self-report measures. We hypothesize that participants in the plain packaging condition will report more negative perceptions of the pack, the cigarettes and their smoking experience than those in the branded packaging condition. Again, we will explore whether these effects are most pronounced among female smokers.

Finally, we will assess the effects of cigarette packaging on the reward value ascribed to tobacco. First, participants will complete a concurrent choice task where they are required to choose between earning two distinct rewards: tobacco and chocolate [11]. Those in the branded pack condition will earn points for their branded pack cigarettes, while those in the plain pack condition will earn points for their plain pack cigarettes. Preferential selection of the tobacco key in this task has been demonstrated to reflect the relative value ascribed to the tobacco versus the chocolate reward. Second, in a transfer task, participants will choose between the two rewards after being presented with either a picture of a branded or plain pack of cigarettes, or no stimulus. Typically, cigarette cues enhance the probability of tobacco choice by approximately 15% [11,12]. We will explore whether branded versus plain packages differ in their capacity to enhance tobacco choice and whether this difference is modulated by the 24-hour exposure to either the branded or plain pack. Any change in the effectiveness of these cues to motivate tobacco choice would arguably be driven by learning about these cues over the 24-hour exposure period.

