### Sample size determination

The sample size for the study has been calculated based on the volume of smoke inhaled by participants, which is one of the primary outcome measures. Previous data collection using these topography monitors from our laboratory indicates a mean inhaled volume per cigarette of 500 ml (SD 100). Therefore, in order to detect a reduction in inhaled volume of 50 ml per cigarette (equivalent to one fewer cigarette per day for a 10-a-day smoker) with 80% power at an alpha level of 5%, we will recruit 128 participants. Given the short-term nature of this study, we expect the number of withdrawals to be low.

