### Data analysis

We will use linear regression to evaluate the effect of cigarette packaging (branded or plain) on the primary and secondary outcome measures using an intention-to-treat analysis. We will run these analyses with and without adjustments for age, sex, heaviness of smoking, and where appropriate, corresponding baseline measures. We will further explore whether sex modifies these effects by including appropriate interaction terms in our models. As noted above, we expect the number of withdrawals from the study to be low. Missing data is most likely to occur due to failure of the smoking topography device. Based on prior experience, this is uncommon and equally likely to occur in both arms of the study.

The concurrent choice and transfer data will be analyzed in two stages. First, a 2 (condition: plain, branded) × 2 (sex: male, female) analysis of variance (ANOVA) will be conducted on the percent choice of the tobacco key in the concurrent training stage to determine if there is a reduced value ascribed to plain versus branded cigarettes. Second, a 2 (condition: plain, branded) × 2 (sex: male, female) × 3 (transfer task cue exposure condition: plain, branded, control) mixed-model ANOVA will examine whether the effectiveness of these cues in motivating tobacco-seeking behavior is influenced by 24-hour exposure to packaging. Interactions will be explored using *post-hoc* tests corrected for multiple comparisons using the Bonferroni method.

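### Two primary outcomes have no rule for how they combine: if either one suffices at 5%, familywise error is up to 9.75%, and the stated 80% power covers inhaled volume only

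*Protocol article*

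**What the plan says.** Outcome measures lists two primary outcomes: "Primary outcome measures will be: (1) smoking behavior across a 24-hour period, defined by the number of cigarettes smoked", and the average volume of smoke inhaled per cigarette from the topography device.

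Sample size determination states that the calculation is "based on the volume of smoke inhaled by participants, which is one of the primary outcome measures". It takes a mean of 500 ml and an SD of 100 ml, aims "in order to detect a reduction in inhaled volume of 50 ml per cigarette", and concludes "with 80% power at an alpha level of 5%, we will recruit 128 participants". It gives no effect size, SD or power for the number of cigarettes.

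Data analysis plans linear regression for the primary and secondary outcomes. It gives no significance level, testing order, alpha split or success rule for the two primaries. Its only multiplicity correction is Bonferroni, applied to post-hoc tests of interactions in the reward-task ANOVAs.

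Two other places bear on the missing rule. Study objectives and hypotheses predicts that the plain-pack group "will smoke fewer cigarettes and will have reduced exposure to cigarette smoke over the course of the day", joining the two effects with 'and'. The Discussion says that a significant fall in consumption would be grounds for a longer trial, and attaches no condition on inhaled volume.

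**The concern.** With two primary outcomes, the type I error and the power of the trial depend on how the two results are combined. The protocol leaves this open, and its own text points two ways. The hypothesis reads as though both effects are expected together. The Discussion draws a consequence from consumption alone, and on its natural reading that is the outcome with no power calculation.

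An undeclared rule can be settled after the results are known. A significant result on one outcome and a null result on the other could be reported as plain packaging changing smoking behaviour, at an error rate above 5%. The trial is meant to inform policymakers, so a false claim on one outcome would matter. The protocol corrects for multiplicity in a secondary outcome, the reward task, which makes its silence on the primaries more conspicuous.

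**Working it through.** **Inputs from the protocol.** Difference 50 ml, SD 100 ml, alpha 5%, power 80%, total 128 (Sample size determination). Equal allocation, so 64 per arm (Randomization).

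**Inputs not in the protocol.** The correlation between the two outcomes and the effect on the count are not given, so both are varied below.

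**1. Reproduce the stated sample size.** Standardised difference d = 50/100 = 0.5. A two-sided two-sample t-test at 5% with 80% power needs 63.8 per arm, rounded to 64, so 128 in total. Power at 64 per arm is 80.1%. A one-sided test would need about 100 in total, so the 5% is two-sided. The stated figure is right for volume alone.

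**2. Error if either outcome suffices, each at two-sided 5%.** Familywise error = 1 − P(|Z1| < 1.96 and |Z2| < 1.96), with Z1 and Z2 bivariate normal. At correlation 0 this is 1 − 0.95² = 0.0975.

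| Correlation | Familywise error |
|---|---|
| 0 | 9.75% |
| 0.3 | 9.5% |
| 0.5 | 9.1% |
| 0.7 | 8.3% |
| 0.9 | 7.0% |

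These figures count one test per outcome.

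**3. Error and power if both are required, each at 5%.** The chance that both are significant cannot exceed the chance that one is, so the error is at most 5% whichever null is true. By the same argument, joint power cannot exceed the 80% for volume. Assuming d = 0.5 on both outcomes, joint power at 64 per arm is 65% at correlation 0, 70% at 0.5 and 76% at 0.9. A smaller effect on the count lowers it further.

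**4. Power for volume if alpha is protected.**
- Plain Bonferroni, 2.5% per outcome: 71.2% by the t-test, 72.1% by the normal approximation. Restoring 80% would take 77.3, so 78 per arm, or 156 in total.
- Holm: volume is significant if its p-value is at most 2.5%, or if it is at most 5% and the count's is at most 2.5%. By the normal approximation, with the count effect between d = 0 and d = 0.5 and correlation 0 to 0.9, power for volume is about 72% to 78%.
- Fixed sequence with volume first at 5%: power for volume stays at 80.1%.

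**The case against.** The strongest reply is that this is an omission from a condensed journal article, and that an analysis plan not shown may set the testing order. That is possible, and silence alone would not be enough. What stands against it is that the article itself fixes two primaries, spends all of the alpha on one of them, sets out multiplicity control for a secondary task, and contains wording that supports two different success rules.

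Three stronger readings are tempting, and the document does not support them.

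- *Each primary is tested at 5%, so the error is 9–10%.* The 5% appears only in the volume calculation, and no text says that either outcome suffices. The figure is conditional. It falls to 7.0% at correlation 0.9, and to at most 5% if both outcomes are required.
- *The 80% power is wrong.* It reproduces exactly, and the section says openly that it concerns one of the primary outcomes. It simply does not describe a joint rule or the count.
- *Joint power is below 30%.* Power of 23–29% for one fewer cigarette follows from an assumed SD of 4.6 to 4.0, where 4.6 is a uniform spread over the eligible 5 to 20 per day. The protocol gives no such SD, and the calculation ignores the planned adjustment for heaviness of smoking and baseline. With an assumed baseline correlation of 0.7 the figure becomes about 40–50%. It is an illustration only.

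It can also be said that putting volume first is a choice: Outcome measures lists the count first, and the Discussion gives weight to consumption. That is fair, and it is why Holm is offered as an alternative.

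**Conclusion.** The concern holds in a conditional form. The protocol names two primary outcomes without saying how they combine, and powers only one.

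- **If either suffices**, as the Discussion allows for consumption, familywise error is up to 9.75%, and between 7.0% and 9.75% for correlations from 0 to 0.9.
- **If both are required**, as the hypothesis suggests, error is at most 5%. The trial's power is then at most the 80% for volume: 65% to 76% under an assumed d = 0.5 on both.

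On neither reading are 5% and 80% together the operating characteristics of the trial. The error range rests on an assumed correlation, and the joint-power range also on an assumed count effect. The sample size of 128 is not in dispute.

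**What to change.** Declare one rule for the two primaries before outcome data are examined. The last participant was enrolled on 11 December 2013 and the article was resubmitted on 27 May 2014, so the declaration should say explicitly that outcome data had not been seen. If they had been, it should say that the rule is post hoc.

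Either of these would serve:

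1. **Holm across the two primaries.** Compare the smaller p-value with 2.5% and, if it passes, the larger with 5%. State power for volume as at least about 71% (the plain Bonferroni level), or about 72–78% depending on the count effect and the correlation.
2. **Fixed sequence.** Test volume per cigarette first at two-sided 5%, since the sample size is built on it, and the number of cigarettes at 5% only if volume is significant. This keeps the stated 80% for volume.

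In both cases, report the 80% (or its replacement) as the power for volume alone with 128 evaluable participants, and align the hypothesis and the Discussion with the chosen rule.

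The cost is wording only, with no extra participants or data. Under Holm, power for volume is somewhat lower. Under the fixed sequence, a significant fall in cigarettes smoked is not confirmatory when volume misses, which would weaken the Discussion's case for a longer trial based on consumption.

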### Data analysis

We will use linear regression to evaluate the effect of cigarette packaging (branded or plain) on the primary and secondary outcome measures using an intention-to-treat analysis. We will run these analyses with and without adjustments for age, sex, heaviness of smoking, and where appropriate, corresponding baseline measures. We will further explore whether sex modifies these effects by including appropriate interaction terms in our models. As noted above, we expect the number of withdrawals from the study to be low. Missing data is most likely to occur due to failure of the smoking topography device. Based on prior experience, this is uncommon and equally likely to occur in both arms of the study.

The concurrent choice and transfer data will be analyzed in two stages. First, a 2 (condition: plain, branded) × 2 (sex: male, female) analysis of variance (ANOVA) will be conducted on the percent choice of the tobacco key in the concurrent training stage to determine if there is a reduced value ascribed to plain versus branded cigarettes. Second, a 2 (condition: plain, branded) × 2 (sex: male, female) × 3 (transfer task cue exposure condition: plain, branded, control) mixed-model ANOVA will examine whether the effectiveness of these cues in motivating tobacco-seeking behavior is influenced by 24-hour exposure to packaging. Interactions will be explored using *post-hoc* tests corrected for multiple comparisons using the Bonferroni method.

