Preferential selection of the tobacco key in this concurrent task has previously been demonstrated to reflect the relative value ascribed to the tobacco versus the chocolate reward. If plain packaged cigarettes are ascribed a lower value than branded cigarettes, we should find reduced tobacco choice in the plain versus branded group. There will be 40 trials of concurrent training in total. At the end of this training participants will be tested for knowledge of the instrumental contingencies through the on-screen questions: ‘Which key earned tobacco/chocolate, the D or the H key? Please choose carefully’. The order of the two questions will be randomized. Participants will then complete a transfer task in which they will choose between the tobacco and chocolate key in the presence of three cue conditions: no stimulus, plain pack, or branded pack. There will be 60 trials in total, blocked into 10 cycles of six trials, presenting two of each of the three cue conditions in random order. In trials where a pack is presented, this pack will be randomly sampled from a set of 100 (comprised of 10 brands × 10 health warnings). The difference between branded versus plain packs in their capacity to enhance tobacco choice, and whether this difference is modulated by the cigarette pack assigned to participants in the 24-hour exposure will be assessed.

Participants will finally be asked about their views on cigarette packaging and plain packaging. On completing the experiment, participants will be fully debriefed and given the opportunity to ask questions. Participants will be reimbursed with £30 for participating in the study.

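### The transfer-task question is a single branded-versus-plain contrast by assigned pack, but the analysis names only a three-cue ANOVA with unlisted Bonferroni post-hoc tests; name the contrast as the planned test

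*Protocol article*

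**What the plan says.** The question is put twice. Under Study objectives and hypotheses, the aim reads "whether branded versus plain packages differ in their capacity to enhance tobacco choice and whether this difference is modulated"; the modifier is the day spent with the assigned pack. The transfer-task description (24-hour pack exposure, Test Day 2) repeats it: "whether this difference is modulated by the cigarette pack assigned to participants in the 24-hour exposure will be assessed".

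The task has "three cue conditions: no stimulus, plain pack, or branded pack". The Data analysis section then plans a mixed ANOVA with condition (2 levels), sex (2 levels) and a cue factor described as "3 (transfer task cue exposure condition: plain, branded, control) mixed-model ANOVA will examine whether the effectiveness of these cues"; the stated aim is to see if the exposure changed that effectiveness. The next sentence adds: "Interactions will be explored using *post-hoc* tests corrected for multiple comparisons using the Bonferroni method". It gives neither the comparisons, nor their number, nor whether they depend on a significant F. No branded-versus-plain contrast is named.

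**The concern.** The enhancement produced by each pack type is measured against no stimulus. In the difference between the two enhancements the no-stimulus level cancels, so the stated question has one degree of freedom: is branded minus plain the same in both arms? The condition-by-cue term of a three-level cue factor has two. Its null is that the arm difference is the same at all three cues.

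Two things follow.

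- A significant interaction may mean only that packs in general work differently from a blank screen in one arm.
- A real branded-versus-plain modulation may be missed, because the omnibus test spreads its attention over two contrasts, pools their error, and is followed by a further correction.

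This is the only analysis given for an objective that the article states in two places.

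**Working it through.** **The plan's own figure.** N = 128 (Sample size determination) is for inhaled volume: a difference of 50 ml, SD 100, 80% power and 5% alpha, taken as two-sided. The normal formula gives 2 × (1.96 + 0.84)² × 100²/50² ≈ 63 per arm. The exact t calculation gives 64 per arm, or 128 in total, with 80.1% power. So N = 128 reproduces. The article gives no power figure for the transfer task.

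**Inputs.** From the article: 128 participants, two conditions, equal sexes (32 per condition-by-sex cell) and three cues. Assumed: SD 25 percentage points per cue, the correlations in the table below, normal data, no dropout, and three comparisons in the Bonferroni step.

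**The two nulls.** Let P, B and C be the arm differences in tobacco choice under plain, branded and no-stimulus cues.

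- Stated question: (B − C) − (P − C) = B − P = 0, 1 df.
- Condition-by-cue term: P = B = C, 2 df, with error df 2 × (128 − 4) = 248.

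If P = B but C differs, the first null is true and the second is false.

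**Effect size.** The direct contrast has noncentrality λ = (128/4) × δ²/σ_D², where δ is the arm difference in branded minus plain and σ_D² = 2 × 25² × (1 − pack-pack correlation). With 1 and 124 df, 80% power needs λ = 7.97, so δ = σ_D × √(7.97 × 4/128) ≈ 0.50 σ_D.

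**Power with equal correlations.**

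- If the two pack cues shift equally in opposite directions and no stimulus is unchanged, λ stays at 7.97 on 2 and 248 df: 71% power. About 22% more participants would restore 80%.
- If only the plain cue moves, the sum of squares is δ² × 2/3 instead of δ²/2, so λ = 7.97 × 4/3 = 10.63: 83.5% power. The omnibus alone then loses nothing.

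**Unequal correlations.** The omnibus error averages the two contrast variances. At pack-pack 0.8 and pack-none 0.6 these are 625 × (1 − 0.8) = 125 and 625 × (0.9 + 1 − 1.2)/1.5 = 291.7, which average 208.3. The branded-versus-plain effect is then judged against 208.3 instead of its own 125.

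**Power by simulation** (20,000 trials per row; δ set so that the direct contrast has 80%). Two-step means a significant omnibus F and then the contrast at 0.05/3.

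| Pack-pack / pack-none correlation | δ (points) | Shift | Omnibus F | Two-step |
|---|---|---|---|---|
| 0.6 / 0.6 | 11.2 | symmetric | 71% | 64% |
| 0.6 / 0.6 | 11.2 | plain only | 84% | 65% |
| 0.6 / 0.4 | 11.2 | symmetric | 61% | 57% |
| 0.6 / 0.4 | 11.2 | plain only | 73% | 61% |
| 0.8 / 0.6 | 7.9 | symmetric | 52% | 48% |
| 0.8 / 0.6 | 7.9 | plain only | 63% | 54% |
| 0.8 / 0.5 | 7.9 | symmetric | 42% | 39% |
| 0.8 / 0.5 | 7.9 | plain only | 54% | 45% |
| 0.9 / 0.6 | 5.6 | symmetric | 26% | 23% |
| 0.9 / 0.6 | 5.6 | plain only | 35% | 29% |

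If the post-hoc contrast were run without waiting for the omnibus F and with its own error term, the correction alone would cut 80% to 65% (three comparisons) or 71% (two).

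**Rejection when branded minus plain is equal in both arms.** Both pack cues were set lower in the plain arm by the same amount, over the same five correlation pairs.

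| Shift of both packs | Omnibus F | Direct contrast | Two-step |
|---|---|---|---|
| 5 points | 19-30% | about 5% | 0.7-1.8% |
| 10 points | 58-78% | about 5% | 1.4-1.6% |

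**The case against.** The strongest reply is that the ANOVA matches the sentence it belongs to. The Data analysis section speaks of cue effectiveness generally, and the objectives close on any change in effectiveness. Effectiveness against no stimulus needs the control level. If both pack types lose their pull in one arm, a significant interaction is the right answer to that question. This stands. The mismatch is with the narrower question stated in the objectives and the task description.

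A reader might infer that the plan would mislead in the 19-78% of trials shown for the omnibus F. The document does not support that, because post-hoc tests are planned. If they include the contrast, false attribution falls to about 1-2%, and with three cues that pair is an obvious one to include. What remains is that the article does not say so. The 10-point shift is also large: it is two thirds of the roughly 15% typical cue enhancement given in the objectives, if that is read as percentage points.

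A reader might also infer that the ANOVA always loses power. It does not: with equal correlations and only one pack cue moving, the omnibus alone loses nothing. The larger losses depend on correlations that the article does not give. That the post-hoc tests wait for a significant F, and that there are three of them, are likewise assumptions.

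Finally, contrast-level detail is often left to an analysis plan, and the task is exploratory. That limits the weight of the point. It does not remove it, because the article does name a specific test and that test is not the one its stated question calls for.

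**Conclusion.** The point holds as a targeting problem in a secondary, exploratory analysis. The 2-df term tests whether cue effectiveness in general changed. The stated branded-versus-plain question has no named test, and it is safe from misreading only if an unlisted post-hoc comparison happens to cover it.

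The two-step route was less powerful than the direct contrast in every pattern checked. Against 80%, it had about 64-65% with equal correlations, 57-61% at correlations of 0.6 and 0.4, and 23-54% in the three settings with pack-pack correlation 0.8 or 0.9. These figures rest on the assumed correlations, three comparisons and gating by the omnibus F; the SD sets the size of δ in points, not the power.

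The primary analyses and N = 128 are not affected. This is an inexpensive improvement, not a flaw that invalidates the transfer task.

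**What to change.** In the Data analysis section, name the test of the stated question. For each participant, take percent tobacco choice under branded cues minus percent under plain cues, and regress this score on condition, sex and condition-by-sex.

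- The condition term tests whether exposure modulates the branded-versus-plain difference.
- The interaction term tests whether sex modifies that modulation.
- The overall mean score tests whether branded and plain cues differ at all.

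State that this does not depend on the omnibus F. Keep the mean of the two pack cues minus no stimulus, together with the ANOVA, for the broader question of cue effectiveness.

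The cost is one or two sentences, with no new data or participants. Each contrast uses its own error term, so sphericity is not needed. The small downside is that the omnibus F is no longer the headline test of the transfer task.
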